### Measurements

The endpoint assessors, who are only responsible for postoperative follow-up, will regularly visit all patients at the planned time points (Table 1). The nurse will check the patients every 4 h. At 10:00 AM every day, the attending neurologist and nurse will evaluate whether the patient experienced symptomatic vasospasm in the last 24 h and record it in the case report form. All patients will receive brain imaging, including CT, CTA, and CTP examination, at least twice, before the operation and 5–8 days after the operation. Postoperative days 5–8 correspond to the peak period of CVS appearance 7–10 days after aSAH. Imaging aims to assess CTA vasospasm, cerebral perfusion, new hemorrhage (if present), and infarction. CT needs to be examined an additional two times, one within 24 h after the operation to assess whether new cerebral infarction or hemorrhage is caused by surgery and one at discharge to assess the occurrence of new cerebral infarction. The assessments will be completed mainly by an independent radiologist. All TCD monitoring will be performed by an experienced and specialized follower on the day before surgery (T0) and on the immediate (T1), 1st (T2), 2nd (T3), 3rd (T4), 5th (T5), 7th (T6), and 9th (T7) days after the operation. Delirium will be documented using the CAM-ICU during the first 3 days after the operation. Additionally, cognitive performance will be assessed at baseline and at 24 h, 7 days, 30 days, and 90 days after surgery using the Mini-Mental State Examination (MMSE). The modified Rankin scale (mRS) will be used to assess patient disability at discharge and at 90 days. The incidence of complications, including myocardial infarction, postoperative rebleeding, moderate and severe brain edema, pulmonary embolism, deep venous thrombosis, SGB-related complications, and unexpected adverse events, will also be recorded. All baseline and intraoperative data will be recorded by the resident anesthesiologists and the attending anesthesiologists who are responsible for recruitment and intervention.

### Primary outcome

The primary efficacy outcome is the incidence of symptomatic vasospasm within 14 days after aSAH, which is defined as new focal or global neurological dysfunction or a decrease in the Glasgow coma score by more than two points, with angiographic vasospasm on TCD or CTA [34–36]. Symptoms must not be explainable by causes such as primary bleeding, rebleeding, hydrocephalus, fever, infection, electrolyte or metabolic disorders, and surgical complications.

### Secondary outcomes

The secondary outcomes in the BLOCK-CVS trial include the following:Incidence of TCD vasospasm within 14 days after aSAH [34].Incidence of CTA vasospasm on days 5–8 after the operation [34].Incidence of abnormal perfusion monitored by CTP on days 5–8 after the operationIncidence of new cerebral infarction observed on days 5–8 after the operation and at dischargeContinuous cerebral blood flow velocity monitored by TCD on the day before surgery (T0) and on the immediate (T1), 1st (T2), 2nd (T3), 3rd (T4), 5th (T5), 7th (T6), and 9th (T7) days after the operationThe Mini-Mental State Examination (MMSE) score was assessed at 24 h, 7 days, 30 days, and 90 days after the operationIncidence of delirium as measured by CAM within 3 days after the operationTotal length of stay in the intensive care unit and hospitalModified Rankin Scale (mRS) score at discharge, 30 days, and 90 daysAll-cause mortality up to 90 daysIncidence of complications up to 90 days

See Supplement Part 3 for detailed definitions of all observed indicators.

### Sample size calculation

At our institution, we have observed a symptomatic vasospasm rate of approximately 45%. The cure rate of SGB in the treatment of progressive CVS was reported as 39% in another trial [31]. Therefore, we hypothesize a positive effect size of 40% for e-SGB compared with the baseline rate. Finally, using PASS 15, a total of 228 patients were needed to detect the difference (27% in the treatment arm vs. 45% in the control arm) in the primary outcome with 80% power and a two-sided alpha of 0.05, allowing for a 5% loss to follow-up. An interim analysis will be performed when 50% of the required sample size is recruited.

### Statistical analysis

All efficacy and safety analyses will be analyzed on both a per-protocol and intention-to-treat basis. The intent-to-treat (ITT) population will comprise all subjects randomized to receive e-SGB and with the completed assessment of symptomatic CVS. The per-protocol (PP) population will consist of all subjects in the ITT population not identified as protocol violators (i.e., no obvious Horner’s syndrome after e-SGB, etc.). These protocol violations will be shown in a listing. Subjects with puncture interruption and abandonment due to various reasons are considered to have failed e-SGB and will be excluded from any form of analysis. The decision to exclude a subject from the PP population will be made prior to breaking the blind. The primary outcome will be compared between groups using the Cochran–Mantel–Haenszel test. Postoperative cerebral hemodynamic changes measured at multiple planned time points will be compared using repeated-measures analysis of variance (ANOVA) with the Tukey–Kramer test. In addition, repeated-measures ANOVA will be utilized with a mixed-model approach (including time as a random effect), and the specific comparison of the change in each of those measurements between baseline and any specific time point will be tested using linear contrast. For other outcome data, categorical data will be analyzed by the *χ*^2^ test, and continuous data will be analyzed using Student’s *t* test or the Mann–Whitney *U* test. The rates of spasm, death, complications, and length of stay in the hospital and intensive care unit will be compared using Cox proportional hazards models. All analyses will be adjusted by age, sex, preoperative Hunt-Hess score, preoperative Fisher grade, and site of aneurysm. For the missing data, the last observation and the worst-case imputation scenarios will be used as the main interpolation method. A *p* value less than or equal to 0.05 (two-tailed alpha level) will be considered statistically significant.

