### Intervention

Randomized patients will receive an additional e-SGB or a “camouflage” operation before anesthesia induction and then receive standard care after the operation. In the intervention group, e-SGB will be performed by a designated experienced anesthesiologist using the B-ultrasound visualization technique. The intervention site will be the ipsilateral side of the planned craniotomy site. After routine disinfection, 8–10 mL of 0.5% ropivacaine will be injected into the surface of the longus colli muscle on the medial side of the prevertebral fascia at the level of the C6 anterior tubercle (Fig. 2), and the puncture point will be covered with sterile dressings. The success criterion of e-SGB is Horner's syndrome, which is characterized by miosis, ptosis, enophthalmos, conjunctival hyperemia, and facial redness without sweating. The patient will be monitored for at least 30 min before anesthesia induction to rule out any related complications after SGB. Patients with failed e-SGB will be excluded. In the control group, a blank control was adopted to reduce unnecessary invasive operations. Patients will not undergo any sham procedures and will only be prospectively visited at a specified time point. However, they need to undergo the “camouflage” operation to ensure the smooth implementation of the blinded endpoint evaluation. The anesthesiologist will cover the corresponding part of the patient with sterile dressings to confuse the follow-up, without any puncture. In this way, the follow-up staff would not be aware of the grouping of the participants by the puncture point. All patients will be admitted to the ICU after the operation and then receive the standard of care.

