### Discontinuation or withdrawal of study subjects

All subjects may voluntarily withdraw from the trial at any time for any reason, and the investigator may also discontinue the participation of any subject for a variety of reasons, primarily safety concerns or protocol violations.

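### The set labelled ITT drops abandoned blocks in the e-SGB arm only and requires a completed outcome assessment, so it is not an intention-to-treat set

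*Protocol article*

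**What the plan says.** All places are in the protocol article.

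- **Statistical analysis, ITT set:** "The intent-to-treat (ITT) population will comprise all subjects randomized to receive e-SGB and with the completed assessment of symptomatic CVS".
- **Statistical analysis, abandoned punctures:** patients whose puncture is interrupted or given up, for whatever reason, count as failed e-SGB and leave every analysis.
- **Statistical analysis, per-protocol (PP) set:** ITT subjects "not identified as protocol violators". Absence of an obvious Horner's syndrome is the example given of a violation. PP exclusions are to be decided before unblinding; nothing similar is said about abandoned punctures.
- **Statistical analysis, missing data:** last-observation and worst-case imputation.
- **Intervention:** Horner's syndrome is the criterion of a successful block, and "Patients with failed e-SGB will be excluded". Controls receive a dressing and no puncture.
- **Randomization and blinding:** the attending anesthesiologist obtains the allocation once the patient is in the operating room. The anesthesiologist and neurosurgeons are not blinded.
- **SGB-related complications:** these complications are safety indicators.
- **Sample size calculation:** "27% in the treatment arm vs. 45% in the control arm", "with 80% power and a two-sided alpha of 0.05", "allowing for a 5% loss to follow-up".

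**The concern.** An intention-to-treat set keeps everyone who was randomised, in the arm assigned, so that the groups differ at the outset only by chance. The set described here departs from that in two substantive ways.

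First, patients leave it because of something that happens after allocation and can only happen under e-SGB. If those whose puncture is given up differ in vasospasm risk from the rest, their counterparts stay in the control arm and the comparison is shifted. The decision to give up lies with staff who know the allocation, and no criterion for it is stated. The removal also covers safety, so a puncture stopped because of a complication would be missing from the analysis meant to detect such complications.

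Second, entry depends on the primary assessment being complete, which is also a post-randomisation event.

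At stake is the primary superiority comparison, together with every other efficacy and safety analysis run on this set.

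**Working it through.** **1. Reproduce the planned sample size.** Inputs from Sample size calculation: 45% versus 27%, 80% power, two-sided alpha 0.05, 5% loss. With unpooled variance:

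n per arm = (1.960 + 0.842)² × (0.45×0.55 + 0.27×0.73) / 0.18² = 7.849 × 0.4446 / 0.0324 = 107.7, so 108.

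108 / 0.95 = 113.7, so 114 per arm and 228 in total. This matches the protocol exactly. The 5% covers loss to follow-up; nothing is allowed for failed blocks.

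**2. Can the exclusion be balanced between arms?** The order is: allocation revealed in the operating room, block attempted, puncture completed or given up. A control has no puncture and so cannot meet the exclusion. It is therefore post-randomisation and one-sided.

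**3. Do the rules agree with each other?**

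| Patient | One rule | Another rule |
|---|---|---|
| Puncture completed, no Horner's syndrome | Intervention: block not successful, failed blocks excluded | Statistical analysis: out of PP, still in ITT |
| Primary assessment incomplete | ITT definition: not in the set | Missing-data rule: impute, but this patient is no longer in the set |
| Puncture abandoned because of a complication | Statistical analysis: out of every analysis | SGB-related complications: a safety indicator |

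**4. Possible size of the bias.** Assumptions, none given in the protocol: no true effect; overall risk 45% in each full arm; 108 per arm; a share f of blocks fails and is removed; risk among failures p_f is 60-70%. The retained e-SGB rate is (0.45 − f·p_f)/(1 − f), on 108(1 − f) patients, compared with 45% on 108 controls. Type I error is from the two-sided two-proportion z-test with pooled null variance (normal approximation).

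Example, f = 10% and p_f = 70%: (0.45 − 0.07)/0.90 = 42.2%, a spurious benefit of 2.8 points.

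| Failed blocks | Spurious benefit (points) | Two-sided type I error |
|---|---|---|
| 2% | 0.3-0.5 | 5.0-5.1% |
| 5% | 0.8-1.3 | 5.2-5.4% |
| 10% | 1.7-2.8 | 5.7-6.8% |
| 20% | 3.8-6.3 | 8.2-14.1% |

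If p_f = 45% the bias is zero at every f. If p_f is below 45% the sign reverses and the exclusion works against e-SGB.

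**5. Power when failures are kept.** Assumption: failed blocks gain nothing (45%) and the others have 27%. The e-SGB rate is 0.27(1 − f) + 0.45f, tested against 45% with 108 per arm by the same test.

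| Failed blocks | e-SGB rate | Power |
|---|---|---|
| 0% | 27.0% | 79% |
| 2% | 27.4% | 77% |
| 5% | 27.9% | 75% |
| 10% | 28.8% | 70% |

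The 79% at no failures, rather than 80%, arises because this test uses the pooled variance and step 1 the unpooled one.

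**The case against.** Several points on the other side are sound.

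- **Failures may be rare.** The block is ultrasound-guided and done by an experienced operator. Eligibility excludes altered neck anatomy, local trauma or infection, coagulation dysfunction and ASA status above III, and limits Hunt-Hess grade to 1-3. All of this points to the lower rows of failure, where the effect on type I error is negligible. This stands as to size; it does not make the set intention-to-treat.
- **The absence of controls from the ITT sentence.** A reader might infer that the ITT set has no control patients. The same section compares the primary outcome between groups, so this is very probably a wording slip.
- **The comparison is not randomised, and the bias favours e-SGB.** A reader might infer both. Neither is supported: with few exclusions the comparison remains largely randomised, and nothing in the protocol links block failure to vasospasm risk.
- **The Horner's conflict.** The Intervention section does not say from what failed blocks are excluded, and the total exclusion in Statistical analysis names only interrupted or abandoned punctures. The two may have been meant to fit together. That leaves an ambiguity to reconcile.
- **Incomplete assessments.** Symptomatic vasospasm is evaluated daily, so a patient who dies early has assessments up to death, and imputation is planned. But the protocol does not say when an assessment counts as completed, and imputation cannot reach a patient outside the set.
- **Discontinuation.** The protocol says "the investigator may also discontinue the participation of any subject for a variety of reasons, primarily safety concerns or protocol violations". A reader might infer that outcomes of violators are discarded. The text does not say so, and after serious SGB complications follow-up is to continue unless withdrawal is requested. This sentence does not carry the point.

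**Conclusion.** The set is wrong as written. Removing abandoned punctures from every analysis is a one-arm, post-randomisation exclusion in unblinded hands, and no other part of the protocol defines an all-randomised set that would offset it. The completed-assessment condition conflicts with the imputation rule beside it, and the handling of blocks without Horner's syndrome must be reconciled between Intervention and Statistical analysis.

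How much this matters numerically cannot be settled from the protocol. Under the assumptions in the working, it is trivial at 2-5% failure, modest at 10% and serious at 20%. Both the higher risk among failures and the failure rates themselves are assumptions, so the direction is open too. The case for changing the definition does not depend on those figures: a superiority claim labelled intention-to-treat should rest on everyone randomised.

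**What to change.** - **ITT, the primary set:** all randomised patients in both arms, analysed as allocated, whatever the puncture outcome, Horner's sign or completeness of assessment. Missing outcomes follow the imputation rule already stated. This also corrects the omission of the control arm.
- **PP only:** failed, abandoned and no-Horner's blocks are excluded here and nowhere else. Remove the exclusion from all analyses, and bring the exclusion sentence in Intervention into line.
- **Safety:** keep every attempted puncture in the safety analysis.
- **Follow-up and reporting:** continue outcome follow-up for these patients, and report failed and abandoned blocks by arm.

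The change is mainly one of wording, but it has costs. Keeping failures dilutes the effect: if they gain no benefit, power is about 77%, 75% and 70% at 2%, 5% and 10% failure, against 79% with none. Recruitment began in July 2021, so outcomes may be unrecoverable for patients already excluded; their number should be reported.

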**Assessments**								
Baseline variables	✖							
Neurological examination	✖		✖	✖	✖	✖	✖	
Physiological parameters	✖	✖	✖	✖	✖	✖	✖	
MMSE	✖		✖		✖		✖	✖
CAM-ICU	✖		✖	✖				
mRS							✖	✖
TCD	✖		✖	✖	✖	✖		
CT	✖		✖		✖		✖	
CTA/CTP	✖				✖			
Complications		✖	✖	✖	✖	✖	✖	✖
All adverse events		✖	✖	✖	✖	✖		
Length of stay							✖	
All-cause mortality							✖	✖

*SGB* Stellate ganglion block, *TCD* Transcranial Doppler, *MMSE* Mini-Mental State Examination, *CAM-ICU* Confusion Assessment Method for the Intensive Care Unit, *mRS* modified Rankin scale, *CT* Computed tomography, *CTA* Computed tomography angiography, *CTP* Computed tomography perfusion imaging

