### SGB-related complications

Complications related to SGB can be greatly reduced by ultrasound-guided procedures. Although the incidence is low, experienced anesthesiologists will be involved, and SGB-related complications will be regarded as safety indicators in this study. Patients who present suspicious symptoms within 30 min after e-SGB will be treated immediately, and a preliminary diagnosis will be graded by the anesthesiologist (Table 2). According to the patient’s condition, the anesthesiologist and the neurosurgeon will decide jointly whether to suspend the operation or implement further treatment. For serious complications (grading criteria ≥ 3), additional follow-up may be required to ensure patient safety; in those cases, the patient will be unblinded, but we will continue follow-up outcomes unless the patient or their families request withdrawal from this study. Serious complications, such as subarachnoid block, will be immediately reported to the ethics committee by the PI, and an emergency data monitoring committee meeting will be initiated for consultation. The possible complications of SGB and the time of observation for each are as follows:Block or injury of nerve: recurrent laryngeal, phrenic, brachial plexus, and vagus nerves (30 min after e-SGB and during hospitalization)Injury of the artery: internal carotid and vertebral arteries (30 min after e-SGB)Local anesthetic poisoning (30 min after e-SGB)Subarachnoid block (30 min after e-SGB)Pneumothorax and hemothorax (30 min after e-SGB)Infection and hematoma at the puncture site (during hospitalization)

**Table 2 Tab2:** Classification of complications

Grade	Definition
Grade 1	No need for drugs or surgery, endoscopy, or intervention
Grade 2	Requiring some treatment, including blood transfusions and parenteral nutrition
Grade 3	Requiring surgical, endoscopic, or radiological intervention
3a	Intervention not under general anesthesia
3b	Intervention under general anesthesia
Grade 4	Severe life-threatening complications need to be transferred to the intensive care unit or special care unit
4a	Single-organ dysfunction
4b	Multiorgan dysfunction
Grade 5	Resulting in death

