### Adverse event monitoring report and data monitoring committee

An adverse event (AE) is the development of an undesirable medical condition/complication or the deterioration of a preexisting medical condition following or during exposure to an intervention, whether considered causally related to the intervention. The expected harm/complications will be systematically collected by visiting each patient at each follow-up point, while the unexpected harm/complications will be collected through spontaneous reporting from the patients or physicians in charge. All study-related AEs will be recorded and closely monitored until they are resolved or stable or until it can be confirmed that the study treatment is not the cause of the events. The investigator will immediately report to the research department and advise the PI to determine the severity of the adverse event as soon as it occurs. In addition, it should be reported to the Ethics Committee (IRB) within 24 h, and the PI is responsible for reporting all AEs. The Data Monitoring Committee (DMC) will be responsible for monitoring clinical safety and reviewing all adverse events reported to the IRB to determine the risks and benefits of the study. The DMC is made up of specialists in anesthesiology, neuropathies, ethics, statistics, and methodology. If there were any severe adverse events (SAEs) associated with the study (grading criteria ≥ 3), the DMC was responsible for discussing whether to terminate the study (Table 2). In this study, all expected AE records will also be used as safety indicators to evaluate the safety of e-SGB, which is mainly completed by the DMC and reported in the final trial publications. If e-SGB significantly increases the risk of certain adverse events or is related to an unexpected SAE that deteriorates the patient’s condition, such as aneurysm rupture and rebleeding before clipping, we will emphasize this in the final results.

If the patient’s health is damaged due to participation in this study, we will be responsible for taking appropriate treatment measures. The sponsor, Beijing Tiantan Hospital, Capital Medical University, will bear the treatment expenses and pay corresponding economic compensation to the patients according to relevant national regulations.

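### Patients whose puncture is interrupted or abandoned are removed from the safety analysis as well as the efficacy analysis, in the e-SGB arm only, so block harms can be under-reported

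*Protocol article*

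**What the plan says.** **Analysis sets (Statistical analysis).** Safety is analysed on the same two sets as efficacy. The intention-to-treat set also requires a completed assessment of symptomatic vasospasm. The per-protocol set drops protocol violators, with absent Horner's syndrome as the example. On failed punctures the section says: "Subjects with puncture interruption and abandonment due to various reasons are considered to have failed e-SGB and will be excluded from any form of analysis".

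**Role of block harms.** The section SGB-related complications says that "SGB-related complications will be regarded as safety indicators in this study". It grades them, gives each an observation time, and keeps following patients after a serious one unless they or their families ask to withdraw. The section on adverse event monitoring uses the records of expected events to evaluate the safety of e-SGB and will report them in the final publications.

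**Timing in Table 1.** The block, the camouflage action and the block data are marked in the Pre column. The complications row and the row "All adverse events" have their first mark in the Dur column.

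**Rebleeding.** The complications listed under Measurements are given as "including myocardial infarction, postoperative rebleeding, moderate and severe brain edema" and further items, ending with unexpected adverse events. The adverse event section describes an unexpected serious event that worsens the patient's condition, "such as aneurysm rupture and rebleeding before clipping". It collects unexpected events through spontaneous reports from patients or treating physicians.

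**The concern.** Half of the trial's hypothesis (Background) is that early block is safe. An exclusion that depends on what happened while the block was being given, and that can touch one arm only, breaks the randomised comparison. If some punctures are stopped because of a complication, the patients removed are those who carry the harm.

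The reasons for interruption are left open, so nothing in the rule keeps such patients in. The planned arm has 228/2 = 114 patients and serious block events are expected to be few, so losing one or two cases could change the safety statement. The requirement for a completed vasospasm assessment adds a second route out: a patient who dies early may have no such assessment and would then leave the safety set even though the block was completed.

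**Working it through.** **1. The plan's own figure.** Inputs from Sample size calculation: "27% in the treatment arm vs. 45% in the control arm", "with 80% power and a two-sided alpha of 0.05", "allowing for a 5% loss to follow-up". With unpooled variance:

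n = (1.960 + 0.842)² × (0.45 × 0.55 + 0.27 × 0.73) / 0.18² = 107.7, so 108 per arm.

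108 / 0.95 = 113.7, so 114 per arm and 228 in total. The stated size reproduces exactly.

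**2. Effect of the exclusion on power.** Two-proportion normal approximation with pooled variance under the null, 114 controls, before any loss to follow-up:

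| e-SGB patients dropped | e-SGB analysed | Power |
|---|---|---|
| 0 | 114 | 81.2% |
| 6 | 108 | 80.1% |
| 11 | 103 | 79.1% |

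Power is not the issue.

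**3. Effect on the reported harm rate.** Let k be the number of interrupted punctures among 114, h the proportion of those with a harm, and c the harm rate in completed blocks.

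- Rate in all attempted blocks: [k·h + (114 − k)·c] / 114
- Rate reported under the exclusion: c
- Difference: k·(h − c) / 114
- Share of harms hidden: k·h / [k·h + (114 − k)·c]

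The rate is understated only if h exceeds c. None of k, h and c is in the documents. Assume c = 2%, k from 1 to 11 (about 1% to 10% of blocks) and h from 20% to 100%. Each cell gives the rate in all attempted blocks, with the share of harms hidden in brackets. The reported rate is 2.0% throughout.

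| k | h = 20% | h = 50% | h = 100% |
|---|---|---|---|
| 1 | 2.2% (8%) | 2.4% (18%) | 2.9% (31%) |
| 2 | 2.3% (15%) | 2.8% (31%) | 3.7% (47%) |
| 6 | 2.9% (36%) | 4.5% (58%) | 7.2% (74%) |
| 11 | 3.7% (52%) | 6.6% (73%) | 11.5% (84%) |

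Worked cell, k = 6 and h = 50%: (3 + 108 × 0.02) / 114 = 5.16 / 114 = 4.5%; hidden share 3 / 5.16 = 58%. At the other extreme, h = 0 and k = 6 gives 2.16 / 114 = 1.9%, so a reported 2.0% would be slightly too high.

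**4. The sections side by side.**

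- *Exclusion against purpose.* Statistical analysis removes these patients from everything. SGB-related complications keeps following them, and the adverse event section needs their records for the safety verdict. These cannot all be carried out.
- *Table against text.* Table 1 marks no adverse-event collection at Pre. Yet Intervention requires at least 30 minutes of monitoring before induction, SGB-related complications sets a 30-minute observation time for most listed harms, and Measurements records them. The table is out of line with the text.
- *Pre-clipping rebleeding.* It is absent from the listed block complications, and Measurements names only the postoperative form. The 30-minute observation is tied to the block, and no matching window is stated for controls.
- *Failed block.* Intervention excludes failed blocks and defines success by Horner's syndrome. Statistical analysis treats absent Horner's syndrome as a per-protocol violation only. These two passages must be reconciled.

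**The case against.** The strongest reply has four parts.

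**Harms are collected.** From the blank Pre cells in Table 1 a reader might infer that harms during the block go unrecorded. The documents do not support that. Monitoring, grading and recording in the first 30 minutes are written into the text, and the definition of an adverse event covers the time of exposure. This objection stands: the blank cells are a mismatch to correct.

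**Harms still reach oversight.** Adverse events go to the ethics committee within 24 hours and to the data monitoring committee. This also stands, so the harms of excluded patients are not lost to safety oversight. But it does not repair the planned analysis, which leaves these patients out.

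**No link between interruption and harm is shown.** A reader might infer that the rate is too low by construction. The article says only that reasons vary, and a harm that appears after a completed puncture is not caught by the rule. Bias is therefore possible, and its size depends on an unknown overlap. The objection limits the claim but does not remove it, because the rule has no exception for a puncture stopped for harm.

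**Rebleeding may be covered elsewhere.** A reader might infer that pre-clipping rebleeding could not be compared between arms. That goes too far: the list under Measurements is open-ended, the anesthesiologist is present in both arms, complications are compared between groups, and the supplement with the definitions is not shown. What remains is that the article itself classes this event with those reported spontaneously.

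**Conclusion.** The point holds for the analysis rule. As written, it removes e-SGB patients from the safety analysis according to what happened during the intervention, has no counterpart in controls, and contradicts two other sections of the same article. It should be changed before the data are analysed.

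The direction is towards a safer-looking block whenever harms are more frequent among interrupted than among completed punctures. The size cannot be derived from the documents; the range of 8% to 84% of harms hidden rests wholly on the assumed values above. The threat is to the validity of the safety estimate and of the intention-to-treat comparison, while power moves by about two percentage points at most in the cases examined.

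The Table 1 rows and the handling of pre-clipping rebleeding are lesser points of alignment and do not show that harms would be missed.

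**What to change.** 1. Delete the sentence that excludes interrupted or abandoned punctures from all analyses. The per-protocol set can still leave these patients out as listed violations.
2. Define the safety set as all randomised patients, analysed by assigned arm, whether or not the block was completed and whether or not the vasospasm assessment was completed. Assigned arm is preferable to a rule based on needle insertion, which would count an e-SGB patient with an event during preparation as a control.
3. In addition, report block-specific complications among all patients in whom a block was attempted.
4. In Table 1, mark the complications and adverse-event rows at Pre, starting at randomisation, in both arms.
5. Record rupture or rebleeding before clipping as a solicited event in both arms.
6. Reconcile Intervention and Statistical analysis on what counts as a failed block and what follows from it.

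The cost is wording, two table marks and one CRF line. The sample size stays at 228. The observed e-SGB complication rate may look less favourable.
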